### Sample size calculation

A total sampling method was used. The sample size was determined based on the primary outcome of postoperative corneal endothelial cell density (ECD) loss, referring to a previous study by Chee et al.
^
14
^ The minimal sample size calculated for this study was 36 subjects for each group (95% confidence interval, power 80%, β = 0.20, α = 0.05, SD = 201 ​​cell/mm
^2^, expected difference = 132 ​​cell/mm
^2^, subjects should have at least 132 ​​cell/mm
^2^ difference of ECD loss after phacoemulsification in the intervention group). With a 10% additional for anticipating loss to follow-up subjects, the minimal sample size needed was 40 for each group.

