### Intervention

Patients will be divided into three groups, each with 40 samples. The first group (n=40) will receive 500 mg oral vitamin C three times daily (1500 mg/day) for one week before surgery to four weeks after surgery. The second group (n=40) will receive 500 mg oral vitamin C three times daily (1500 mg/day) for one week before surgery and a placebo after surgery. The last group (n=40) will receive a placebo one week before surgery to four weeks after surgery. Oral vitamin C 1500 mg/day was chosen based on pharmacokinetic evidence showing that this dosage can achieve stable plasma concentrations and approach a steady-state level during short-term administration.
^
15
^

To minimize potential bias related to surgical variability, all phacoemulsification procedures will be performed using standardized surgical techniques. The surgeries will be conducted by experienced cataract surgeons using the same phacoemulsification machine and standardized operative settings. Key intraoperative parameters, including ultrasound power, irrigation parameters, and the type of ophthalmic viscosurgical device (OVD), will be standardized across all procedures.

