### Statistical analysis

Data from this study will be recorded and analyzed by IBM SPSS 20.0. Sample personal identification, including demographic and clinical characteristics, will be reported in a descriptive analysis. Data distribution of numerical variables will be assessed using the Shapiro–Wilk test with normal distribution will be presented as mean (standard deviation [SD]); non-normal distribution will be reported as median (interquartile range [IQR]). Nominal data will be reported in frequency and percentage. We will use Pearson’s chi-squared test for categorical data. For comparisons among the three groups, one-way ANOVA will be used for normally distributed data, while the Kruskal–Wallis test will be used for non-normally distributed data. Significant group differences will be followed by post-hoc pairwise comparisons using Bonferroni correction for ANOVA or Dunn’s test following the Kruskal–Wallis analysis to account for multiple testing. Pearson’s test will be used to test the correlation between data in aqueous humor and serum. A p-value of less than 0.05 (p < 0.05) will be considered statistically significant.

Effective phacoemulsification time (EPT) and total surgical duration will be included as covariates in the statistical analysis to account for their potential influence on postoperative endothelial outcomes. Multivariable analysis will also be conducted to control for potential confounding variables, including smoking status, occupational exposure, ultraviolet (UV) light exposure, and dietary intake of vitamin C. These variables will be collected through structured questionnaires during the screening.

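### The stated 80% power matches one unadjusted two-group comparison; under the planned Bonferroni step each pairwise comparison has about 64%

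*Protocol article*

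**What the plan says.** Under Sample size calculation, the protocol article bases the size on loss of endothelial cell density (ECD). Its inputs are "power 80%, β = 0.20, α = 0.05, SD = 201" and "expected difference = 132" (both in cells/mm²). It concludes: "The minimal sample size calculated for this study was 36 subjects for each group (95% confidence interval, power 80" per cent. Allowance for loss follows: "With a 10% additional for anticipating loss to follow-up subjects, the minimal sample size needed was 40 for each group". The section mentions neither the number of arms nor any multiplicity adjustment, and it does not say which test the calculation assumes.

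Under Intervention there are three arms: "Patients will be divided into three groups, each with 40 samples". They are vitamin C before and after surgery (pre+post), vitamin C before surgery only (pre-only), and placebo.

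Under Statistical analysis the first step is an overall test: "For comparisons among the three groups, one-way ANOVA will be used for normally distributed data", with Kruskal–Wallis as the non-normal alternative. Then: "Significant group differences will be followed by post-hoc pairwise comparisons using Bonferroni correction for ANOVA", or Dunn's test after Kruskal–Wallis. Nowhere is one pair named as primary or exempted from the correction.

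**The concern.** The sample size rests on one difference and one SD at α 0.05, as for a two-arm trial with a single test. The analysis instead tests three arms overall and then compares three pairs, each at 0.05/3. A power figure worked out for the first procedure does not describe the second.

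What is at stake is how non-significant results are read. A reader who takes 80% at face value will assume that a true difference of 132 between two arms would be missed one time in five. Under the planned pairwise procedure it would be missed more than one time in three. The risk of over-reading is greatest for pre+post against pre-only. The introduction gives a separate rationale for postoperative dosing, and only that contrast isolates it, yet no expected size is stated for it.

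**Working it through.** **Inputs.** From Sample size calculation: difference δ = 132, SD σ = 201, α = 0.05, power 80%, 36 analysed and 40 enrolled per group. From Intervention: three equal arms. From Statistical analysis: overall test at 0.05, then Bonferroni over pairs. Three arms give three pairs, so each pair is tested at 0.05/3 = 0.0167. Sidedness is not stated and is inferred in step 1.

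**1. The plan's own figure.** For two groups, two-sided:

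n = 2(z₀.₉₇₅ + z₀.₈₀)² σ²/δ² = 2 × (1.960 + 0.842)² × 201²/132² = 2 × 7.849 × 2.319 = 36.4

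This is 36 rounded down, or 37 rounded up. The one-sided version gives 29, so two-sided is the reading that fits. The loss allowance also reproduces: 36/0.9 = 40.

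**2. Power of that single comparison at 36 per group.** Standard error = 201 × √(2/36) = 47.4. Standardised difference = 132/47.4 = 2.786. Normal approximation: Φ(2.786 − 1.960) = 79.6%. Noncentral t, 70 df: 78.5%.

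**3. Power per pair at 0.0167.** The normal critical value is 2.394, so Φ(2.786 − 2.394) = 65.3%. The t results are:

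| Analysed per group | t, two-sample df | t, ANOVA-pooled df | Normal approximation |
|---|---|---|---|
| 36 | 63.1% | 63.8% | 65.3% |
| 40 | 68.8% | 69.4% | 70.6% |

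Simulating the planned sequence (F test at 0.05, then Bonferroni pairs; 40,000 trials) gives about 64% at 36 per group for a pair that truly differs by 132. The overall gate therefore costs almost nothing beyond the Bonferroni step.

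**4. Power of the overall ANOVA.** Noncentrality λ = n Σ(μᵢ − μ̄)²/σ².
- Means 0, 0, 132 (or 0, 132, 132): Σ = 44² + 44² + 88² = 11,616, so λ = 36 × 11,616/40,401 = 10.35. Power is 81.8% at 36 per group (85.9% at 40).
- Means 0, 66, 132: Σ = 66² + 66² = 8,712, so λ = 7.76. Power is 69.0% at 36 per group (74.0% at 40).

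**5. Pre+post against pre-only.** The document gives no expected difference. Assume half of 132, that is 66. Standardised difference = 66/47.4 = 1.393. Normal approximation: Φ(1.393 − 2.394) = 15.8%; by t, about 15%. If the difference were instead the full 132, step 3 applies and power is about 64%.

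**6. For scale.** 80% power per Bonferroni pair would need 2 × (2.394 + 0.842)² × 2.319 = 48.6, so 49 analysed per group, or 50 by t with pooled df.

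**The case against.** The strongest reply is that the first planned test is the overall one and the pairwise tests are follow-up. On that reading 80% is not badly wrong. The ANOVA has about 82% power when two arms are equal and the third differs by 132. If both vitamin C arms work equally, the chance of showing at least one better than placebo is about 79% under the full sequence. This stands. A reader might infer that the trial as a whole is underpowered, and the figures do not support that. But the 82% depends on the pattern of means and falls to 69% if the middle arm lies halfway. A significant overall test also does not say which regimen differs.

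A reader might also infer that the protocol promises 80% for each regimen against placebo. It does not; it speaks of the intervention group in the singular and leaves the comparison undefined. Nor does it follow that the trial has almost no power for pre+post against pre-only: the 15% rests on an assumed half effect that appears nowhere in the document.

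The 64% takes 36 as analysed. With no losses it is about 69%, still short of 80%. Adjusting for effective phacoemulsification time and surgical duration might add power, but no correlation is given from which to estimate the gain. Correcting for only two pairs would give about 69% at 36 per group, but the text does not restrict the pairs.

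Finally, one might call the Bonferroni step unnecessary, because with three arms unadjusted pairs after a significant overall test hold the family-wise error for one variable at one visit. That is no error in the plan: Bonferroni is conservative but valid. The Study status section puts the trial in data processing, so loosening the correction now would be hard to defend. A claim of 5% family-wise error would also ignore that the primary outcome has two forms and four visits.

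**Conclusion.** The point holds in a limited form. The 80% describes one unadjusted, two-sided, two-group comparison. It does not describe the Bonferroni-corrected pairwise comparisons the article plans, which have about 64% power each with 36 analysed per group and about 69% with 40. The overall ANOVA does reach about 82% at 36 per group in the favourable patterns, and 69% if the middle arm lies halfway.

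These figures take the document's difference and SD as true and assume equal arms, correction over all three pairs, normal data (the ANOVA branch) and no gain from covariates. The two-group reading is an inference from the formula that reproduces 36. Type I error is not inflated and no bias arises; the fault is a power statement that does not match the analysis. The difference between 36 and 37 is trivial.

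**What to change.** In Sample size calculation, add wording such as: *The 80% refers to a single unadjusted, two-sided comparison of two groups. For a true difference of 132 cells/mm² (SD 201), each Bonferroni-corrected pairwise comparison has about 64% power with 36 analysed per group and about 69% with 40. A non-significant pairwise result must not be read as evidence of no effect. This includes pre- and postoperative against preoperative-only vitamin C, where power is about 15% with 36 analysed per group if the difference is assumed to be 66 cells/mm².*

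It would help to give the overall ANOVA figures beside it (about 82% or 69% at 36 per group, according to the pattern of means).

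Keep the Bonferroni correction in Statistical analysis as it stands.

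The cost is a less favourable stated power. No patients are added and no test changes.

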^ Oral vitamin C may represent a practical antioxidant due to its wide availability and lower risk of adverse effects compared with other antioxidant strategies such as intravenous vitamin C and intracameral antioxidants. Regarding these findings, we hypothesized that oral vitamin C supplementation increases ascorbic acid levels and overall antioxidant capacity in the aqueous humor and reduces oxidative stress–related endothelial damage during phacoemulsification. However, to date, no clinical studies have specifically evaluated the protective role of oral vitamin c supplementation in patients with hard cataracts undergoing phacoemulsification. On the other hand, aqueous humor will also be replaced by irrigation fluid during phacoemulsification, which may reduce the intraocular antioxidant content. Therefore, oral vitamin C is given postoperatively to restore AA levels in the aqueous humor. Thus, it is expected that the antioxidant effect of AA can suppress postoperative corneal endothelial autophagy and apoptosis, which can cause severe damage to the endothelial layer. Considering that aqueous humor sampling cannot be performed during the postoperative recovery period, it is important to determine whether the levels of MDA, TCA, and AA in the aqueous humor are the same as or correlate with blood levels, as no studies have yet examined these three biomolecular parameters simultaneously in both compartments.

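### The stated 80% power is an unadjusted two-group figure for one unnamed contrast; it describes neither the planned three-arm pairwise tests nor the Group 1 vs Group 2 comparison.

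*Protocol article*

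**What the plan says.** The Sample size calculation section gives one set of inputs: "power 80%, β = 0.20, α = 0.05, SD = 201" cells/mm², and "expected difference = 132" cells/mm². The outcome is postoperative ECD loss. The result is 36 evaluable per group, raised to 40 for 10% loss to follow-up. The difference ("subjects should have at least 132 ​​cell/mm"²) is tied to one intervention group, in the singular, and the pair it describes is not named. The alpha carries no adjustment for multiple comparisons.

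The Randomization and Intervention sections describe three groups of 40. Group 1 takes vitamin C before and after surgery. Group 2 takes it "for one week before surgery and a placebo after surgery". Group 3 takes placebo throughout. Group 2's active treatment is therefore the preoperative part of Group 1's course.

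The Introduction gives the postoperative phase its own rationale, namely that irrigation fluid replaces the aqueous humor during surgery: "Therefore, oral vitamin C is given postoperatively to restore AA levels in the aqueous humor".

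The Statistical analysis section plans a three-group ANOVA or Kruskal–Wallis test, then pairwise tests: "Significant group differences will be followed by post-hoc pairwise comparisons using Bonferroni correction for ANOVA", or Dunn's test after Kruskal–Wallis.

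**The concern.** A reader who meets one 80% power figure in a three-arm trial will tend to attach it to whichever pairwise result is in front of them. Two features of the plan prevent that. First, the pairwise tests are corrected for multiplicity and the sample size is not. Second, the arms are nested, so the three pairwise differences are linked and cannot all equal 132.

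The contrast most exposed is Group 1 vs Group 2, the only one that addresses the postoperative rationale. If postoperative vitamin C supplied half of a 132 benefit, this comparison would still most likely be non-significant. Set beside a stated 80% power, that result could be taken to show that continuing after surgery adds nothing.

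**Working it through.** **Inputs.** SD 201, difference 132, alpha 0.05, power 80%, 36 evaluable and 40 randomised per group (Sample size calculation); three equal groups (Intervention); Bonferroni over three pairs, 0.05/3 = 0.0167 (Statistical analysis). Sidedness is not stated outright. Two-sided is inferred from "36 subjects for each group (95% confidence interval" and because a one-sided formula gives 29, not 36.

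**1. The plan's own figure.** n = 2(1.96 + 0.84)² × (201/132)² = 36.4 per group. Strict rounding up gives 37; the plan prints 36. Power at 36 is 79.6% by the normal formula and 78.5% by the t test. Dropout: 36/0.9 = 40. Both printed figures are reproduced as an unadjusted two-group calculation.

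**2. A true difference of 132 under the planned correction.** The standard error of a difference is 201 × √(2/n), which is 47.4 at n = 36 and 44.9 at n = 40. The noncentrality is 132/47.4 = 2.79 at 36 and 132/44.9 = 2.94 at 40. Two-sided t-test power:

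| Difference 132 | n = 36 | n = 40 |
|---|---|---|
| alpha 0.05 | 78.5% | 82.7% |
| alpha 0.0167 | 63% | 69% |

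**3. How the three differences are linked.** (G1 − G3) = (G1 − G2) + (G2 − G3). Suppose G1 − G3 is a benefit of 132 and neither phase does harm. The two steps are then non-negative and sum to 132, so the smaller is at most 132/2 = 66. The even split is the most favourable case for the weaker step. G1 vs G2 reaches 132 only if the preoperative week contributes nothing, or if the full course gains more than 132 (264 if each step is 132).

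**4. Power at 66.** Noncentrality is 66/47.4 = 1.39 at 36 and 66/44.9 = 1.47 at 40.

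| Difference 66 | n = 36 | n = 40 |
|---|---|---|
| alpha 0.05 | 28% | 31% |
| alpha 0.0167 | 15% | 17% |

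With an uneven split the smaller step has less: at 44 (a third of 132) it has 15% uncorrected at n = 36.

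**5. Difference detectable with 80% power.** At 36 per group, 134.6 uncorrected and 156.5 with Bonferroni. At 40 per group, 127.5 and 148.2.

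**6. The whole procedure.** For ECD benefits of 132/66/0 in Groups 1, 2 and 3 with 36 per group, ANOVA power is 69%. Simulating ANOVA followed by Bonferroni (100,000 runs) gives 63% for Group 1 vs Group 3 and 15% for each step. If both vitamin C groups gain 132 over placebo, ANOVA power is 82%.

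**The case against.** A reader might infer that the protocol promises 80% power for every pair, or that its sample size is miscalculated. Neither is supported. No sentence claims 80% for all three pairs, and the 36 and 40 reproduce. Sizing a trial on its main contrast, with the other pairs as post-hoc tests, is ordinary practice. The aims and hypothesis read most naturally as vitamin C against no vitamin C.

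The 28% figure is also conditional. It becomes 31% if all 40 are evaluable, and it assumes that neither phase does harm. It bounds the smaller step, which need not be Group 1 vs Group 2: if the preoperative week did little, the postoperative step would be the larger one. If both vitamin C groups gain 132, there is no true Group 1 vs Group 2 difference to miss and the ANOVA keeps 82% power. Adjusting for phacoemulsification time and surgical duration, as planned, could raise power by an amount the document does not allow one to calculate. Nor does the document say that a non-significant Group 1 vs Group 2 result would be read as no benefit.

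All of this stands, and it limits the point to what the power statement covers. It does not make the 80% apply to the tests the plan specifies: even the most natural contrast, at the full 132, falls to 63–69% under the stated Bonferroni correction. It also gives Group 1 vs Group 2 no power statement of its own, although the Introduction argues specifically for the postoperative phase.

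**Conclusion.** The concern holds as a misapplied power statement. The 80% belongs to one unnamed pair with a true difference of 132, tested at an unadjusted two-sided 0.05. Under the planned Bonferroni comparisons that pair has about 63% power at 36 per group and 69% at 40. The 80% does not carry over to Group 1 vs Group 2. With a total gain of 132 and no harm from either phase, the smaller step has at most about 28% power at 36 (31% at 40) uncorrected, and 15% (17%) corrected.

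These figures rest on SD 201, normally distributed outcomes, unadjusted t tests and a Group 1 vs Group 3 difference of 132. The last is an assumption, because the document does not assign 132 to a pair. Uncorrected, the problem with the steps comes from the effect size alone; the multiplicity correction is a second, separate reduction.

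**What to change.** In Sample size calculation:
- Have the sponsor name the vitamin C vs placebo contrast that 132 cells/mm² describes.
- Restate its power under the planned test: about 63% at 36 and 69% at 40 per group with Bonferroni.
- State that Group 1 vs Group 2 is not powered at 80%, with a detectable difference at 36 per group of about 135 uncorrected and 157 with Bonferroni.

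In Statistical analysis:
- Report Group 1 vs Group 2 as a mean difference with a 95% confidence interval.
- State that non-significance there will not be read as absence of a postoperative benefit.

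The article reports that the study is already in data processing, so this is a change of wording and reporting. It needs no extra enrolment or data. The cost is a less favourable stated power and a more cautious claim for the postoperative comparison.

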### Participants

The target population of this study is patients with hard nucleus cataracts who undergo phacoemulsification. Patients are eligible to be included in this study with the following inclusion criteria: aged above 60 years, have senile cataract in one or both eyes with Lens Opacities Classification System (LOCS) III nuclear opacity grade 4-6 and nuclear color grade 4-6, willing to consume prescription and participate in the study follow up for seven weeks starting from recruitment, and signed the informed consent. Written informed consent was obtained from all participants prior to enrollment in the study.

The exclusion criteria of this study are as follows: patients with vitamin C allergy or sensitivity, undergo intraoperative complications of postoperative infections, have corneal endothelium disorder, history of intraocular surgery, glaucoma, trauma, or other intraocular inflammations, have diabetes mellitus and kidney disorders, or consumes vitamins as daily supplements.

Samples will be dropped out during the study if they did not participate in the study follow-up or consume less than 80% of the prescribed medications.

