**Methods:**

This study is a double-blinded randomized controlled trial. Samples will be divided into three groups, and 500 mg vitamin C three times daily (1500 mg/day), or placebo will be received for seven weeks. Clinical characteristics, ascorbic acid, malondialdehyde, and total antioxidant capacity of patients in serum and aqueous humor will be measured before and after intervention and phacoemulsification.

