### Post-intervention evaluation

Patients will be asked to come a week after screening. Firstly, they asked the side effects of the supplementation, including gastrointestinal disorders (nausea, diarrhea, epigastric pain). Second blood samples will be then drawn to measure post-intervention serum AA, MDA, and TAC.

Sampling for oxidative stress in the aqueous humour will be performed twice, pre- and post-phacoemulsification. During surgery, after the initial incision, 0.2 mL of aqueous humor will be taken using a 1 cc syringe with a 30 G cannula. Phacoemulsification will then be conducted using standard operating procedure to intraocular lens implantation. Another 0.2 mL of aqueous humor will then be taken three minutes after removing the viscoelastic as a post-phacoemulsification sample. This sampling volume is within the range commonly used in aqueous humor biomarker studies and is considered safe under surgical conditions. Because the sampling will be performed through the surgical incision and the anterior chamber will subsequently be maintained with a balanced salt solution, anterior chamber stability will not be affected.
^
16,
17
^ The pre-phacoemulsification aqueous humour samples will be analysed for ascorbic acid (AA), total antioxidant capacity (TAC), and malondialdehyde (MDA), while the post-phacoemulsification samples will be analysed for MDA levels only. Intraoperative parameters, including effective phacoemulsification time (EPT) and total surgical duration, will be recorded for each procedure. All patients will receive topical medications: levofloxacin 5 mg/mL every three hours for one week, prednisolone acetate 10 mg/mL every three hours for 1 week, and tapered down in 4-6 weeks.

Every patient will be evaluated one day, one week, four weeks, and six weeks post-phacoemulsification to measure study parameters and signs of complications, i.e. inflammation or infection. Patients who experience side effects or complications, including toxic anterior segment syndrome (TASS) or endophthalmitis during the duration of follow-up will be exempted from the study and managed according to the standard operational procedure of the Department of Ophthalmology, Faculty of Medicine, University of Indonesia.

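### Randomised patients are removed for events after randomisation and no stated analysis restores them, so the primary ECD comparison is made on a selected subset

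*Protocol article*

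**What the plan says.** Three statements in the protocol article take patients out:

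- Participants, on follow-up and adherence: "Samples will be dropped out during the study if they did not participate in the study follow-up or consume less than 80" (the figure is a percentage of the medication prescribed).
- Participants, among the exclusion criteria: patients who "undergo intraoperative complications of postoperative infections" (the second-last linking word presumably means *or*).
- Post-intervention evaluation: "Patients who experience side effects or complications, including toxic anterior segment syndrome (TASS) or endophthalmitis during the duration of follow-up will be exempted". The sentence goes on to say that they "will be exempted from the study and managed according to the standard operational procedure", so they leave the study and not only the treatment.

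Assigned treatment in the first group runs "for one week before surgery to four weeks after surgery" (Intervention), and the other two groups also start a week before surgery. Aims sets the primary outcome as ECD loss at day 1 and weeks 1, 4 and 6 after surgery. Statistical analysis compares the three groups by one-way ANOVA or Kruskal–Wallis and names no analysis set. Sample size calculation gives 36 per group, raised to 40: "With a 10% additional for anticipating loss to follow-up subjects".

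On treatment duration, the abstract says that vitamin C "or placebo will be received for seven weeks", which differs from the Intervention section.

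**The concern.** Randomisation makes the three groups comparable at the moment of allocation. Each removal rule acts later, on something that happens once treatment has begun. Two kinds of removal could carry information about the result. Surgical complications, toxic anterior segment syndrome and endophthalmitis are plausibly linked to endothelial damage, which is what the trial measures. Adherence and side effects are plausibly linked to the arm, since the article itself asks about gastrointestinal side effects of the supplementation.

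If those patients leave and are not analysed, the primary comparison becomes one of adherent, complication-free completers. It no longer estimates the effect of being allocated to vitamin C, and its p-value loses the protection of randomisation. Once a patient has left, later ECD values may never be measured, so an analysis plan written afterwards could not recover them.

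**Working it through.** **1. Order of events.** Randomisation comes first, then one week of assigned treatment, then surgery, then visits to week 6. Set against this order:

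| Reason for removal | Earliest time it can be known |
|---|---|
| Under 80% intake | during treatment |
| Side effects | during treatment |
| Intraoperative complication | at surgery |
| Postoperative infection or complication | after surgery |
| Missed follow-up | after allocation |

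None can be known at allocation. The section on randomisation says that data are analysed once the minimum required number is reached. It does not say whether that number counts patients randomised or patients remaining.

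**2. The plan's own sample size.** Inputs: difference 132, SD 201, α = 0.05 (two-sided assumed), power 80%.

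n = 2 × (1.960 + 0.842)² × 201² / 132² = 36.4 per group. The article states 36 (rounding up gives 37). Then 36 / (1 − 0.10) = 40. The stated figures reproduce, so this point does not rest on an arithmetic error.

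**3. What the 10% allowance covers.** It is stated for loss to follow-up only. Ten per cent of 40 is 4 patients per group for all reasons together. Power (normal approximation) = Φ(132 / (201 × √(2/n)) − 1.96):

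| Assumed total removal per group | n left | Power |
|---|---|---|
| none | 40 | 83.6% |
| 10% | 36 | 79.6% |
| 15% | 34 | 77.3% |
| 20% | 32 | 74.8% |
| 30% | 28 | 69.1% |

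**4. Bias, as an illustration.** Let a fraction f of one arm be removed, and let the mean ECD loss of those removed differ from those kept by k SDs. The mean of the kept patients then differs from the full-arm mean by f × k × 201. The article gives neither f nor k; both are assumed.

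| f | k | Shift (cells/mm²) | Share of 132 | Type I error |
|---|---|---|---|---|
| 10% | 0.5 | 10.1 | 8% | 5.5% |
| 10% | 1.0 | 20.1 | 15% | 7.1% |
| 20% | 0.5 | 20.1 | 15% | 7.1% |
| 20% | 1.0 | 40.2 | 30% | 13.6% |

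The type I error takes no true effect, 36 per group and SE = 201 × √(2/36) = 47.4. The sign depends on which arm loses patients and whether they did better or worse.

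**5. Power if everyone is analysed.** With 40 per group and assumed non-adherence of 10% or 20% in the vitamin C arm, with no effect in those patients, the difference falls to 132 × 0.9 = 118.8 or 132 × 0.8 = 105.6. Power is then 75.3% or 65.2%.

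**6. Denominator of the 80% rule.** At three doses a day, seven weeks is 3 × 7 × 7 = 147 doses, and one week plus four weeks is 3 × 7 × 5 = 105 doses. Taking every one of 105 doses is 105/147 = 71% of 147, below the 80% line. The same patient could pass or fail depending on which statement is used.

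**The case against.** The strongest reply is that the article never names an analysis set. It condenses a fuller protocol, the flow diagram is not shown, and a separate plan may define an all-randomised analysis. That is fair: use of the reduced set is an inference. But the removal rules themselves are stated, not left open. Patients leave the study, nothing in the article provides for measuring ECD after they leave, and nothing restores them.

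A second reply is that surgeons, examiners, laboratory analysts and participants are blinded and surgery is standardised. This limits discretionary removal and makes arm-related intraoperative complications less likely. It does not stop selection through side effects, adherence or complications tied to the outcome. Removal unrelated to arm would narrow the population without necessarily biasing the contrast.

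Third, restoring patients may not restore power: 65.2% with all 40 per group under 20% non-adherence, against 74.8% with 32 per group and no dilution. This stands as a cost of the fix.

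Some stronger readings are tempting but unsupported:

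- A reader might infer that side effects vanish from the safety data. They are asked about at the one-week visit, and each participant has a logbook for adverse effects (Laboratory analysis). At most, follow-up after removal is lost.
- A reader might infer that every removal reason depends on the arm, or that gastrointestinal effects will be commoner on vitamin C. The article says neither.
- A reader might take the side-effect rule to remove every patient with mild nausea. The sentence follows the postoperative visits and gives serious examples, so its reach is unclear.

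**Conclusion.** The point holds: the article states removal rules that act after randomisation, and following them puts the primary ECD comparison on a selected subset. The conclusion rests on the stated rules together with the absence of any all-randomised analysis in the article. A fuller plan that provides such an analysis would answer part of it, but not the loss of later measurements.

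The size and direction of the bias are unknown. The range of about 10–40 cells/mm² (8–30% of the target difference) rests wholly on assumed rates of 10–20% one-arm removal and differences of 0.5–1 SD. It shows what is possible and does not predict the result. A reader might infer that the trial will overstate the benefit of vitamin C; the documents do not support a direction.

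The conflict over treatment duration is a separate, plain contradiction that leaves the 80% rule without a fixed denominator. The seven weeks in Participants and in the randomisation section refer to follow-up; only the abstract applies them to treatment.

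**What to change.** 1. Make the primary analysis all randomised patients in their allocated group, regardless of adherence, side effects or complications. Use every ECD value recorded at the four postoperative visits, for example in a mixed model, so that a patient with a missed visit still contributes.
2. Limit exclusion criteria to facts known before randomisation.
3. Report removals by arm and reason, and list by arm any randomised patient without surgery or without a postoperative ECD value. Do not make having had surgery a silent entry condition.
4. Keep the set with at least 80% adherence and no complications as a sensitivity analysis.
5. Study status says that the trial was already in data processing in September 2025, so later ECD may not exist for patients already removed. Use what was recorded, state the missing-data assumption, and test it, for instance by giving patients with missing values an ECD loss worse by 0.5 to 1 SD (about 100 to 201 cells/mm²), separately by arm.
6. Reconcile the treatment durations in the abstract and Intervention, and state the denominator of the 80% rule.

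The cost is mainly rewording and returning patients to the dataset. The downside is a possibly diluted effect, with power of about 65–75% at 40 per group under the assumed 10–20% non-adherence, and a result that leans on a missing-data assumption where measurements stopped. Nothing here concerns how side effects or complications are treated, or whether study medication is stopped.
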